## Methods

### Study Design

In this randomized controlled trial (RCT), we will examine the impact of the Caring Contacts intervention delivered through SMS text message across a large, diverse sample of veterans and service members who are stressed (external factors) or distressed (internal factors). This trial is conducted entirely online and will recruit veterans and service members (N=510). To ensure that all participants experiencing stress or distress have access to needed resources (enhanced usual care), each participant, regardless of condition, is provided a tailored set of resources to match their needs (eg, housing, finances, employment, food insecurity, and socialization). Participants are stratified based on whether they endorsed SI in the past year and randomly assigned to 1 of 3 study conditions, including receiving either Caring Contacts, EMA, or both, for the 12-month study period. Given that the frequency of messages and the self-monitoring process inherent to EMA may have its own effect on our outcome variables, we included a Caring Contacts–only condition to isolate the effects of Caring Contacts and EMA. The study design and methods were evaluated during an acceptability and feasibility pilot study, during which we also developed a web-based app platform custom-made for Caring Contacts (manuscript in preparation). The study staff worked with employees housed within a local veteran service organization and an outpatient psychiatry clinic to develop study procedures and the Caring Contacts intervention. From this feedback and use data, adjustments to the protocol, intervention, and EMA procedures were made before the launch of this RCT.

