### Randomization

A randomization module with participants stratified into 2 levels (recent suicidality vs no recent suicidality) and randomized into 3 conditions (Caring Contacts with EMA, Caring Contacts alone, and EMA alone) was built into REDCap. Recent suicidality is indicated by a participant endorsing that they have either wished they were dead or had thoughts of killing themself sometime in the past year. This module is programmed to randomize participants with no involvement of study staff to prevent potential bias, with intervention and control assignments distributed evenly across participants. Once participants have completed the online baseline survey, they are randomized into 1 of the 3 conditions (Table 1; Figures 1 and 2). Further details on the EMA procedures are provided in subsequent sections.

**Table 1 table1:** Assessment and intervention message timeline^a^.

Study procedure		Study condition		
		CC^b^ and monthly EMA	CC only	Monthly EMA only
Consent and baseline survey		✓	✓	✓
Two weeks of baseline EMA^c^		✓	✓	✓

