Caring Contacts is not designed as an automated intervention but explicitly presumes a human-in-the-loop who is choosing the messages and when they should be sent, as well as individually responding to replies from the recipients. Technology facilitates this process but does not replace it. For this study, the message schedule was determined by the lead staff, who have extensive experience with Caring Contacts, including a previous trial and our pilot work. All messages are signed with a nickname chosen by the study staff, and participants are invited (but not directly asked) to reply to the messages. The study staff respond during business hours and provide support and assistance in accessing resources as requested by the participants. The study team responds in a way that fits their personal communication style and accommodates the participant’s communication preferences, including conversation initiated by the participant. All participants are reminded that the research study team does not monitor messages outside of regular business hours and is not able to provide crisis response services.

To facilitate our assessment of Caring Contacts mechanisms, the messages are scheduled to vary across the 7-day month 1 to 12 EMA blocks, with 5 messages falling within the EMA blocks, where the impact on subsequent EMAs that day can be measured, and 5 messages outside of the EMA blocks to minimize the likelihood of participants perceiving Caring Contacts and EMA as linked. (The remaining 3 messages are holiday messages—New Year’s, Veterans Day, and their birthdays—that fall on set days and cannot easily be scheduled to fall either during or outside of the EMA periods.) Further details on the EMA procedures are found in subsequent sections.

If a participant’s reply to a Caring Contacts message indicates distress or suicidality, study staff will reply with support and validation and, as appropriate, offer crisis or other resources. If the participant is in a suicidal crisis, a “warm handoff” to 988 or another crisis line is also offered. If there is a situation involving imminent suicide risk (ie, a participant indicates they are planning a suicide attempt or have a lethal weapon) and they refuse to speak with 988 or other crisis response, research staff and licensed clinical staff or faculty consult to determine the appropriate action.

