For aim 4, to examine potential mechanisms of Caring Contacts, we will use the within-EMA period data and examine within-participants mediation using dynamic structural equation modeling (with random intercepts and slopes) [130]. Dynamic structural equation modeling allows for the simultaneous estimation of within- and between-person effects that allow for idiographic mechanistic models over time, which can be ideal for answering questions about within-participant mechanisms of suicide outcomes. In line with recommendations for intensive longitudinal data analysis, all hypothesized mechanism variables (ie, mattering, personal and social responsibility, perceived burdensomeness, and entrapment) will be centered at both the between-person and within-person mean level. Then, within-person regression models will be run to examine the relationship between the hypothesized mechanisms and suicide outcome, using a lag-1 model and autoregressive covariance structure to account for assessments closer in time to be more highly correlated. Next, to examine the mediation effect of treatment condition on outcomes through the hypothesized mechanisms, we will estimate within-level indirect mediation effects, calculated as the product of the within-level effect of treatment condition on the mechanism (a path) and the effect of the mechanism on the suicide outcome. All mediation analyses will be examined at the within-person level (1-1-1), excluding cross-level mediation. Random starts will be used for all models to replicate the best log-likelihood. Finally, to examine the immediate versus delayed impact of the timing of Caring Contacts intervention, we will use autoregressive modeling to examine the direct impact on stress, distress, and suicide outcomes immediately following a Caring Contacts message compared to times without a message, using the EMA data. For all regressions, 95% CIs will be reported, and statistical significance will be set at *P*<.05.

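### The aim 4 mediation takes randomised condition as a within-person (1-1-1) predictor, but condition is constant within each person, so the a path and the indirect effect are not identified as specified

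*Protocol article*

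**What the plan says.** All of the aim 4 mediation is set out in the last paragraph of the protocol article's Analysis Plan:

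- Data and model: "we will use the within-EMA period data and examine within-participants mediation using dynamic structural equation modeling".
- Purpose: "to examine the mediation effect of treatment condition on outcomes through the hypothesized mechanisms".
- Indirect effect: the product of "the within-level effect of treatment condition on the mechanism (a path) and the effect of the mechanism on the suicide outcome".
- Level: "All mediation analyses will be examined at the within-person level (1-1-1), excluding cross-level mediation".

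A separate final step in the same paragraph uses autoregressive models for the direct effect of a message, comparing moments just after one with moments without one.

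On assignment, Randomization says: "Once participants have completed the online baseline survey, they are randomized into 1 of the 3 conditions". Study Design says participants are "randomly assigned to 1 of 3 study conditions, including receiving either Caring Contacts, EMA, or both, for the 12-month study period". Table 1 shows three parallel columns and no crossover.

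**The concern.** A 1-1-1 mediation needs a predictor, a mediator and an outcome that all vary from moment to moment within a person. The mechanisms and the suicide items do. Condition does not: each participant has one value for the whole year. The plan therefore names a predictor that lives at level 2, asks for its effect at level 1, and excludes the cross-level route by which a person-level predictor could reach a repeatedly measured mechanism. These three statements cannot all hold.

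Mechanisms are one of the trial's four aims and part of its claim to novelty. If the text stays as it is, the analysts must choose after data collection between two different questions: the effect of being randomised to Caring Contacts, or the momentary effect of receiving a message. The two differ in who contributes, in precision and in causal standing, since only the first is a randomised comparison.

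**Working it through.** No stated figure is in dispute; the question is one of identification.

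**Inputs.** N = 510 in 3 conditions, so 510 / 3 = 170 per arm under even allocation. Two arms have EMA in all 12 months: 2 × 170 = 340, which matches the Analysis Plan. An EMA week has 3 × 7 = 21 prompts, and 12 × 21 = 252, which matches Power and Sample Size. Table 1 places a message inside the EMA week in months 1, 3, 4, 7 and 12 for Caring Contacts plus EMA, and in month 12 for Caring Contacts only.

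**Step 1: within-person variation of condition.** Let C_i be condition for person i. At every post-randomisation prompt t, C_ti = C_i, so C_ti − mean_t(C_ti) = 0. Laying out the Table 1 design prompt by prompt gives a within-person variance of 0.0, a maximum deviation from the person mean of 0.0, and a within-level design column of rank 0. The same holds inside each monthly block. All the variation is between persons: for the two monthly-EMA arms, 0.5 × 0.5 = 0.25. The within-level a is not identified, so a × b is undefined for each mechanism. This follows from the design. It does not depend on centring condition, which the plan does not propose (it centres only the mechanisms).

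**Step 2: what an uncentred fit would return.** Take M_ti = g0 + a·C_i + u_i + e_ti. With equal numbers of prompts per person, the estimate of a is the difference between arms in person means. In a simulation of 340 people × 21 prompts with a true difference of 0.4 (30 runs, ordinary random-intercept model), the coefficient and the arm difference in person means both averaged 0.397. So a is a between-person quantity. The planned product would then be a_between × b_within. That is not a within-person indirect effect, and it equals the between-person one, a_between × b_between, only if b_within = b_between.

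**Step 3: what does vary within person.** Message timing does. A message indicator, coded for illustration as 1 for two prompts in each in-block week, has a within-person variance of about 0.02, so its a path is estimable. Scheduled in-block messages:

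- Caring Contacts plus EMA: 170 × 5 = 850.
- Caring Contacts only, month 12: 170 × 1 = 170.
- Total: 1,020, plus any of the three fixed-date messages that fall in a block.
- EMA only: 0. The indicator is always 0, so this arm adds nothing to the within-person message contrast.

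**Step 4: precision of the level-2 a path.** For 170 v 170 and two-sided α = .05, minimum detectable d = (z_0.975 + z_power) × √(2/170).

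- 80% power: (1.960 + 0.842) × 0.1085 = 0.30.
- 95% power: (1.960 + 1.645) × 0.1085 = 0.39.
- Power is 0.45 at an assumed d = 0.2 and 0.79 at an assumed d = 0.3.

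These figures concern the a path alone. The aim 4 sample sizes in Power and Sample Size come from a cited simulation whose inputs are not given, so they cannot be reproduced here.

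**The case against.** The best defence is that condition is a loose word for message exposure. The design supports this: messages were deliberately placed in and out of EMA weeks to study mechanisms, "with 5 messages falling within the EMA blocks, where the impact on subsequent EMAs that day can be measured". If that was meant, 1-1-1 without cross-level paths is coherent and only the predictor's name is wrong. This stands as one possible repair. As a reading of the text it does not. Elsewhere the article uses condition for the randomised arm, including a dummy-coded condition variable with EMA only as reference in the growth model. Message timing has its own step, described in other words and aimed at direct effects rather than mediation.

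Two other rescues are weaker. Coding condition 0 before and 1 after randomisation would create within-person variation, but the article does not say so, gives the baseline EMA another purpose, and such a switch would be confounded with time. Dynamic structural equation modeling does accept person-level predictors of random intercepts and slopes, but mediation by that route is cross-level, which the plan excludes. Nor is this detail left to an analysis plan that is not shown: the article states the predictor, the level and the exclusion, and they conflict.

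A reader might infer more than the article supports:

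- That the analysis cannot run, or would return nothing about Caring Contacts. Step 2 shows that an uncentred model fits and its a coefficient is a genuine randomised contrast; the faults are the label and the product.
- That aim 4 fails as a whole. It does not: the other two parts are estimable.
- That message information comes only from the combined arm. Table 1 also gives the Caring Contacts-only arm an in-block message at month 12.

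**Conclusion.** The point holds for the mediation step of aim 4. With condition fixed per person, its within-person variance is exactly 0, and the within-level a path and the indirect effect are not identified for any mechanism. This needs no distributional assumption, only that condition means the randomised arm, as it does elsewhere in the article.

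The mechanism–outcome regressions, the message-timing analysis and the primary aims (1.1 and 1.2, by analysis of covariance) are untouched. The figures of 850 and 1,020 messages and the 170 v 170 contrast assume full, even enrolment and no pauses, opt-outs or missed prompts. The d of about 0.30 is for the a path alone. It does not show that aim 4 is underpowered; it shows that the stated basis, 510 participants with 252 assessments each, does not describe either workable model, because monthly EMA comes from 340.

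**What to change.** Before analysis, state which effect is wanted and match the model to it.

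- **(a) Effect of randomised condition.** Place condition at level 2 and estimate the between-person indirect effect (2-1-1 or 2-2-2). Remove both the restriction to 1-1-1 and the exclusion of cross-level mediation; 2-2-2 is barred by the first, 2-1-1 by both.
- **(b) Momentary effect of a message.** Keep 1-1-1, but replace condition with a time-varying indicator of message receipt before the prompt, followed by the lagged mechanism and then the later outcome. State that the message contrast comes from the Caring Contacts plus EMA arm and month 12 of the Caring Contacts-only arm. The EMA-only arm can inform only the b path and time trends.
- **Or both**, as separately named models.

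Restate the aim 4 power basis for the model chosen.

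The cost is wording; no new data are needed. The downside of (a) is precision, since a 170 v 170 between-person contrast is less precise than a within-person effect. The downside of (b) is that it is no longer a comparison of randomised arms.

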**Figure 1 figure1:**
[figure not shown]
Example of an ecological momentary assessment with Caring Contacts (“EMA with CC”) month (ie, months 1, 3, 4, 7, and 12) wherein a CC message is delivered within the EMA period.

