**Figure 2 figure2:**
[figure not shown]
Example of an ecological momentary assessment without Caring Contacts (“EMA without CC”) month (ie, months 2, 6, 9, and 11) wherein a CC message is delivered outside the EMA period.

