### Caring Contacts Intervention

Participants randomized to receive the Caring Contacts intervention will receive 13 nondemanding, caring messages over 12 months on the following schedule: a welcome message (following their baseline assessments), one message every 3 to 5 weeks for the first 21 weeks, and one message every 8 to 9 weeks for the last 31 weeks. In addition, participants will receive messages on New Year’s Day, their birthday, and Veterans Day. The delivery day and time of each message vary throughout the year to follow a more naturalistic communication pattern and avoid appearing mechanistic or spam. Table 2 provides the examples of messages.

**Table 2 table2:** Examples of Caring Contacts messages.

Message types	Examples
General	“Hey, this is Alex just checking in. I hope you are doing okay! Feel free to let me know how things are going if it helps.”
Seasonal	“Sending you warm wishes for a bright year ahead! [figure not shown] I am grateful to be in touch with you and hope this new year will be a good one, even as the seasons change – Alex”
Birthday	“Happy Birthday, Sam!! Here’s to another year  I hope you will enjoy the day!”
Veterans Day	“Happy Veteran’s Day, Sam Thank you for volunteering for service. What you’ve done is greatly appreciated. I know that this time can be difficult, if you need someone please reach out, we’re here for you if you need us. – Alex”

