For those participants who will complete EMA for all 12 months (n=340), we will conduct an *exploratory analysis* of changes over time in the mean and intraindividual SD of suicide outcomes. The unique and intensive sampling approach of EMA allows for fine-grained exploration of if and when outcomes change in a clinical trial. Specifically, we will first visually examine trajectories by condition to determine the shape of change *trajectories* over time. Then, following the determination of the shape, we will conduct a linear mixed effects growth model (eg, linear, nonlinear quadratic, and piecewise) [126-129], including a dummy-coded condition variable (with EMA only as the reference) as a predictor of both intercept and slope to determine how intervention condition impacts change in suicide outcomes over time.

For aims 1.2 and 3, to examine secondary suicide outcomes and measures of psychological distress, we will use analysis of covariance to examine condition-specific differences in continuous scores of suicide ideation and cognitions and examine group differences at 12 months, controlling for baseline values of the outcome variable of interest. Similarly, preplanned post hoc comparisons will compare (1) any Caring Contacts (combined) to no Caring Contacts, (2) Caring Contacts with and without EMA, and (3) EMA with and without Caring Contacts. For both aims 1.1 and 1.2, any baseline variables that were not successfully randomized will be included as covariates in the regression models.

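### The aim 4 message-timing contrast does not separate the message effect from drift over the year and the EMA week, or from residual effects of other messages

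*Protocol article*

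**What the plan says.** Table 1 and the legends of Figures 1 and 2 (Randomization) fix the schedule for the whole Caring Contacts plus EMA arm. In five months the message lands inside the EMA week ("ie, months 1, 3, 4, 7, and 12) wherein a CC message is delivered within the EMA period"). In four it is sent that month but not in the EMA week ("months 2, 6, 9, and 11) wherein a CC message is delivered outside the EMA period"). Months 5, 8 and 10 have no scheduled message. The Caring Contacts Intervention section gives the purpose of the split, "with 5 messages falling within the EMA blocks, where the impact on subsequent EMAs that day can be measured", and describes the three holiday messages as ones "that fall on set days and cannot easily be scheduled to fall either during or outside of the EMA periods".

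The last part of aim 4 in the Analysis Plan sets out to tell immediate from delayed effects of a message. It does so with autoregressive models that contrast outcomes "immediately following a Caring Contacts message compared to times without a message, using the EMA data". The text names no month or day term, sets no interval after a message before a prompt counts as message-free, and gives the EMA-only arm no role, although it does not exclude that arm.

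The exploratory growth model is a separate analysis, specified as "including a dummy-coded condition variable (with EMA only as the reference) as a predictor of both intercept and slope".

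**The concern.** The schedule is common to the arm, so whether an EMA week contains a scheduled message is fully determined by study month. The message weeks are, on average, earlier than the others. If scores drift over the year for any reason, that drift enters a comparison of post-message prompts with all other times. Within one week, prompts after a message are necessarily later than prompts before it, so drift over the week enters a same-week comparison. Study Design itself allows that repeated self-monitoring may change the outcomes. A lag-1 autoregressive structure handles correlation between neighbouring prompts; it does not remove either drift.

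The reference times also include EMA weeks in months 2, 6, 9 and 11. If a message sent outside the week still acts during it, the reference contains the delayed effect that the analysis is meant to distinguish from the immediate one.

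Real-time message effects are among the trial's leading claims (Objective; Significance), and the regressions are to be judged at P<.05.

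**Working it through.** **1. The article's own counts.** 12 months × 7 days × 3 prompts = 252 observations, as in Power and Sample Size. 510 × 2/3 = 340 participants with monthly EMA, or 170 per arm. Messages: 5 inside EMA weeks + 4 in months 2, 6, 9 and 11 + 1 welcome + 3 holiday = 13, which agrees with "will receive 13 nondemanding, caring messages over 12 months". Counting the welcome message as the fifth message outside the EMA weeks is an inference, but the total fits. The article gives no effect size or power for the message-timing analysis.

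**2. Imbalance in month.**
- Weeks with a message: (1 + 3 + 4 + 7 + 12)/5 = 27/5 = 5.4.
- Other weeks: (2 + 5 + 6 + 8 + 9 + 10 + 11)/7 = 51/7 = 7.3.
- Gap: 1.9 months. Against all twelve weeks it is 6.5 − 5.4 = 1.1 months.
- The correlation of the in-week indicator with month is −0.27, and 22% of random five-month choices would be at least as early. The imbalance is modest.

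**3. Bias from drift over the year.** For a linear trend of b points per month, the bias against the other seven weeks is b × (5.4 − 7.286) = −1.886b. Higher scores mean higher risk, so a benefit is negative. Assumed trends:

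| b per month | Bias |
|---|---|
| −0.02 | +0.04 |
| −0.05 | +0.09 |
| −0.10 | +0.19 |

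A falling trend hides a benefit; a rising one imitates it.

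**4. Simulation of the literal contrast.** Assumptions: 170 per arm; true immediate effect −0.20 on the two remaining prompts of the message day; message day varied between day 2 and day 6; no carry-over; full response; 60 repetitions. The reference is every other prompt.

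| b per month | Pooled contrast | After differencing against EMA-only at matched slots |
|---|---|---|
| 0 | −0.20 | −0.19 |
| −0.05 | −0.14 | −0.20 |
| −0.10 | −0.08 | −0.20 |

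Arithmetic check: the reference has 5 × 19 = 95 prompts from message weeks and 7 × 21 = 147 from the others. Its mean month is (95 × 5.4 + 147 × 7.286)/242 = 6.55. At b = −0.05 the expected value is −0.20 + 0.05 × 1.15 = −0.14.

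**5. Drift over the week.** Split 21 consecutive prompts after prompt k. The mean position is (k + 1)/2 before and (k + 22)/2 after, so the gap is always 21/2 = 10.5 prompts, or 3.5 days. An assumed drift of 0.02 or 0.05 points per day gives 3.5 × 0.02 = 0.07 or 3.5 × 0.05 = 0.175 points. If only the two remaining prompts of the message day count as post-message, a message after the first prompt of day 4 puts them at mean position 11.5, against 5.5 for the ten earlier prompts. That is 6 prompts or 2 days, and 0.05 per day then gives 0.10. In the pooled contrast this component depends on where in the week messages fall.

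**6. Carry-over.** Add an assumed residual effect of −0.10, from the day after a message to the end of its week and, for a random half of participants, throughout the EMA weeks of months 2, 6, 9 and 11. The pooled contrast becomes −0.16, −0.11 and −0.05 for the three trends. Differencing against EMA-only gives −0.16 to −0.17: the trend is gone, the dilution is not.

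**The case against.** The strongest reply is that a journal article condenses the plan. The contrast is said to use the EMA data without restricting the arm, the stated question points towards time since message, and covariates and exposure coding can be left to the full analysis plan. This has weight, but the article does state a comparator, and that comparator is the weak part.

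The Discussion also names the prompts just before and just after a message as one view of the effect. A same-week comparison holds month constant and recovered −0.19 to −0.20 in every simulated scenario. That answers drift over the year. It does not answer drift over the week, which the simulation did not include. Delivery days vary, so day-in-week terms can be estimated, but varying the day does not remove the drift if those terms are left out.

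Several stronger readings are tempting and are not supported:
- *The growth model is confused with time.* It already uses EMA only as the reference for intercept and slope, so a common trend cancels. Messages also thin out by design, so a benefit that thins with them is arguably the true effect of the schedule as delivered.
- *The EMA-only arm would also remove carry-over.* An arm without messages cannot do that (step 6).
- *Prompts after holiday messages are counted as message-free.* The article does not say so. These are Caring Contacts messages with platform time stamps and can be coded as such.
- *All four out-of-week messages contaminate that month's EMA week.* Figure 2 is not shown, so whether the message precedes or follows the week cannot be read.

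**Conclusion.** The point stands for the aim 4 message-timing analysis only. As worded, its comparator lets change over the year and over the EMA week into the estimated message effect, and can include residual effects of messages sent outside the EMA weeks.

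The early weighting is modest. Over the year, the bias is about 1.1 to 1.9 times the monthly trend, depending on which weeks form the reference. Its direction follows the trend: falling scores would hide a benefit, so a reader should not infer that drift necessarily produces a false positive. Within a week the sign reverses, because post-message prompts come later: a fall over the week would look like a benefit.

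The trend, the immediate effect of −0.20, the carry-over of −0.10 and the weekly drift are all assumptions; the article gives none of them. The primary 12-month comparisons do not use this contrast and are untouched.

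**What to change.** Change the wording of the message-timing analysis in the Analysis Plan (aim 4):

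1. Include the EMA-only arm, giving its participants the same scheduled month, day and prompt slots as reference times. Add month and day-in-week terms, and estimate the message effect as the between-arm difference in change. This removes time trends but not carry-over.
2. Define exposure as time since the last message of any kind (inside the EMA week, outside it, welcome or holiday), taken from the platform time stamps described under Caring Contacts via SMS Text Message Platform. This deals with carry-over and matches the stated question of immediate against delayed effects.

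The growth model needs no change; an indicator for a message in that week could be an optional exploratory sensitivity analysis.

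The cost is a few extra model terms and some precision: differencing two equal arms multiplies the standard error by about √2 = 1.4, in line with the simulation (for example 0.042 against 0.030 at b = −0.10 without carry-over). The EMA data and time stamps are already being collected, and the message schedule stays as it is. The wording should be settled before the data are analysed.
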